## 2. Materials and Methods

### 2.1. Research Design

A randomized controlled trial will be conducted to respond to the following hypothesis: a personalized web-based intervention based on the prevention and management of late effects of cancer treatment will be more effective in improving quality of life of long-term breast cancer survivors and self-efficacy for the management of late sequelae of cancer by primary care providers in long-term breast cancer survivors than conventional primary health care.

Participating subjects will be randomly assigned to the 2 treatment groups: the intervention (the CUMACA-M programme) and control groups (standard care in nursing consultation). The name of CUMACA-M refers to care beyond breast cancer in its original Spanish name (CUidados Más Allá del Cáncer-Mama).

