### 2.5. Sample Size

For the calculation of the sample size, a primary outcome measure, quality of life (QOL), was selected [28]. The QOL measure used for this study goes from 1 (extremely poor) to 10 (excellent). A Cohen’s d of 0.4 (effect size) was established, taking into account a difference in quality of life of 0.75 and a standard deviation of 1.8. This effect size has been established, taking into account previous studies [29], and is expected to occur over time, after the intervention. For its part, the type I error has been set at 5% and the type II error at 20%. According to these parameters, 91 subjects will be needed in the intervention group (IG) and 91 subjects in the control group (CG). Depending on the proportion of losses that may occur, the sample size will be increased, calculating an adjusted sample size. In the event that the pilot study suggests making modifications in the calculation of the sample size due to a re-estimation of the effect size, the appropriate corrections will be made before beginning the study. In this study, sample size estimation was performed using the Granmo Calculator, available online in several languages (https://www.imim.cat/ofertadeserveis/software-public/granmo/) (accessed on 15 May 2022.).

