### 2.6. Randomization and Allocation Concealment

The randomization will be by blocks, and this will be divided by the number of subjects in each block (health center). Six primary health centers will participate, so that, in each block/health center, the sample will be 32 subjects (16 IG and 16 CG). This would be a total of 192 participants, which would cover the calculated sample size of 182 subjects).

A list of random numbers generated by the EpiInfo 7.1 programme will be used to randomly assign participants to groups and to minimize the variation in external factors that can affect the comparison. The randomization method will be masked; therefore, the researchers who perform the randomization will not know to which group each subject will be assigned. To mask the randomization process, sealed and opaque envelopes will be sequentially numbered.

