### 2.10. Data Analysis

The statistical analysis of the data will consist of a descriptive presentation of the parameters analyzed in the CUMACA-M programme. Continuous variables will be described as the mean and standard deviation. Categorical variables will be presented as frequencies and percentages. Subsequently, after assessing the normality of the data, corresponding inferential analyses will be performed. During the first stage, an assessment of the homogeneity of the groups (IG and CG) will be carried out by comparing the outcome variables (QOL and self-efficacy), sociodemographic variables, and clinical variables. For this, Student’s t test will be used for the quantitative variables, the chi-square test for the nominal or dichotomous variables (with the corresponding Fisher’s correction, if necessary), and the Wilcoxon test for variables of an ordinal nature. In a second stage, the differences in the outcome variables between the 2 groups (IG and CG) over time (T0, T1, T2, and T3) will be analyzed using multivariate analysis (MANOVA), in which the “group” factors will be incorporated and “time”, as well as the interaction between the 2. In all cases, the significance level will be set at 0.05. The data will be analyzed with the help of SPSS 24.0 software (IBM, Chicago, IL, USA, 2022)).

The intervention will be considered effective if the two variables evaluated (quality of life and self-efficacy) show results of improvement in the intervention group compared to the control group.

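### The only between-arm test named, a MANOVA of the outcome variables, does not match the rule that quality of life and self-efficacy must both improve

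*Protocol article*

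**What the plan says.** Section 2.1 hypothesises that the programme "will be more effective in improving quality of life of long-term breast cancer survivors and self-efficacy for the management of late sequelae" than conventional primary care. Section 2.10 turns this into a decision rule: "The intervention will be considered effective if the two variables evaluated (quality of life and self-efficacy) show results of improvement in the intervention group", compared with control.

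The between-arm analysis over T0 to T3 is given in one sentence of section 2.10: the differences in the outcome variables "will be analyzed using multivariate analysis (MANOVA), in which the “group” factors will be incorporated and “time”, as well as the interaction between the 2", with significance set at 0.05 throughout. Earlier in the same paragraph the outcome variables are identified as QOL and self-efficacy, and section 2.8 lists the same two as the dependent variables.

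Section 2.5 bases the sample size on QOL only: "a primary outcome measure, quality of life (QOL), was selected", "taking into account a difference in quality of life of 0.75 and a standard deviation of 1.8", with 5% type I and 20% type II error, giving 91 per arm. Section 2.6 plans six centres of 32, which is 192 women or 96 per arm.

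**The concern.** The claim to be made is a conjunction. Its null hypothesis is that at least one of the two outcomes does not improve. A MANOVA with both outcomes as dependent variables tests a different null, that neither outcome differs, and it has no direction. Rejecting it shows that some outcome, or some weighted combination, differs between arms. It does not show that both moved in the intended direction.

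A programme that helped QOL and left self-efficacy unchanged, or the reverse, would fail the stated success rule and could still give a significant result on the one named test. What counts as improvement on each outcome has no test tied to it, so the step from the MANOVA to the conclusion is open. Much rests on that conclusion: section 2.12 makes later access for the control group depend on effectiveness for QOL and self-efficacy, and section 4 ties regional adoption to it.

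**Working it through.** **1. The plan's own sample size.** d = 0.75/1.8 = 0.417. With two-sided alpha 0.05 and 80% power, n = 2(1.960 + 0.842)² × 1.8²/0.75² = 90.4, so 91 per arm. The stated figure is reproduced, for QOL alone.

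**2. Inputs that the article does not give (assumed).** Correlation r between the two outcomes, 0 to 0.7; correlation between visits, 0.3 to 0.7; the effect either constant from T1 or building linearly to T3; complete data. The QOL effect is 0.417 SD and the self-efficacy effect is zero, so the both-outcomes claim is false.

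**3. Joint test at one visit.** For a two-group MANOVA (Hotelling's T²), the noncentrality is λ = (n/2) δ′Σ⁻¹δ. With δ = (0.417, 0) this is (n/2) × 0.417²/(1 − r²). At n = 91, 45.5 × 0.1736 = 7.90, divided by (1 − r²):

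| r | λ | Chance of significance |
|---|---|---|
| 0 | 7.90 | 70% |
| 0.3 | 8.68 | 75% |
| 0.5 | 10.53 | 83% |
| 0.7 | 15.49 | 95% |

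The null outcome does not protect against rejection. When it is correlated with QOL, it makes rejection more likely.

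**4. Joint group-by-time test over T0 to T3** (two outcomes × three changes from baseline, 6 df), 91 per arm, range over r = 0 to 0.7:

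| Visit correlation | Constant effect T1–T3 | Linear build-up to T3 |
|---|---|---|
| 0.3 | 54–87% | 41–73% |
| 0.5 | 71–96% | 56–88% |
| 0.7 | 93–99.9% | 82–99% |

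At 96 per arm, the constant-effect row at visit correlation 0.5 is 74–97%. With an assumed 20% loss (0.8 × 96 ≈ 77 per arm), the lowest row for linear build-up falls to 34–64%.

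**5. Adding a direction check.** Suppose success meant a significant joint test plus both point estimates favouring the programme. At one visit the one-outcome effect passes in 35% (r = 0) to 47% (r = 0.7) of trials at 91 per arm. Simulation at 96 per arm with visit correlation 0.5 to 0.7 and r from 0.3 to 0.7 gives 42–51% for the interaction and 32–48% for the group term.

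**6. Requiring each outcome to be significant** (two-sided 0.05, favouring the programme). The same one-outcome effect passes in 1.9–2.4% of trials without baseline adjustment at 91 per arm. With baseline adjustment at 91 to 96 per arm it passes in about 2–2.5%.

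**7. Power of that rule when both effects are 0.417 SD**, 91 per arm, no dropout:
- Unadjusted: 64% (r = 0; check: 0.80² = 0.64) to 71% (r = 0.7).
- Baseline-adjusted, visit correlation 0.5: the standard error shrinks by √(1 − 0.5²) = 0.866, giving 81–85%.
- Baseline-adjusted with 77 per arm: 71–77%.
- Unadjusted, about 109 (r = 0.7) to 119 (r = 0) per arm would be needed for 80%.

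**The case against.** The strongest reply is that the plan never makes the MANOVA the deciding test. It states a separate success rule, and that rule is correctly worded as needing both outcomes. A reader might infer from the percentages in steps 3 and 4 that the trial would falsely declare success most of the time. The document does not support that. With a real QOL effect the MANOVA's own null is false, so those percentages are its power and not a false-claim rate to set against 5%. Even the 35–50% figure needs a rule (significance plus favourable point estimates) that the article does not state.

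Second, group, time and their interaction could describe a multivariate repeated-measures analysis run for each outcome separately. Then each outcome would have its own test and the mismatch would largely disappear. The text does not exclude this. Still, a multivariate analysis of outcome variables that the same paragraph names as QOL and self-efficacy reads more naturally as joint.

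Third, follow-up tests and thresholds may sit in a fuller plan. That is fair, and their absence is not the point here. The article itself fixes both a test and a decision rule, and on the natural reading the first cannot deliver the second.

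Finally, the size depends on assumed correlations, effect shape and retention. That stands, and it is why the range is wide.

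**Conclusion.** The point holds as a mismatch between the stated test and the stated success rule. A joint MANOVA cannot establish improvement on both outcomes, whatever the correlations. How often the gap would matter is uncertain. With an effect on QOL only and complete data, the joint group-by-time test is significant in about 41–100% of trials at 91 to 96 per arm (71–97% for a constant effect at visit correlation 0.5). A plausible but unstated reading of the success rule would then wrongly pass roughly 35–50%, against about 2–2.5% if both outcomes must be significant. This is not a finding that the plan prescribes a rule with that error rate. If a separate analysis per outcome was intended, saying so and requiring significance on each would settle the matter.

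**What to change.** In section 2.10, make the deciding analysis one baseline-adjusted model for each outcome (QOL-CS total and SEMCD). Name one between-arm contrast in advance, the same for both, for example the T3 difference or the average over T1 to T3. Declare the programme effective only if both contrasts favour it at two-sided 0.05. Because both are required, neither needs a multiplicity adjustment. The MANOVA can stay as a descriptive supplement.

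The rewording and the second model cost little and need no new measurements. The real cost is power. Section 2.5 should say that its 80% applies to QOL alone, and should report the power for both outcomes from step 7: about 81–85% at 91 per arm with baseline adjustment at visit correlation 0.5, 64–71% unadjusted, and lower with dropout. These figures assume that self-efficacy also improves by 0.417 SD, an effect for which the article gives no figure. If that power is judged too low, the sample size review already foreseen after the pilot is the place to deal with it.

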### 2.12. Ethical Considerations

This project has been approved by the Clinical Research Ethics Committee of Navarra (PI_2021/18), and the necessary institutional authorization will be obtained to carry out the study. All participants in Phases II and III of the study will receive an information sheet about the research, their degree of involvement, the treatment of the data, and the legal requirements. Likewise, they will receive, in paper format, the informed consent (shown as supplementary materials) that they must sign if they agree to participate, voluntarily, in the research. Furthermore, participants will be informed that they can leave the study at any time without having to justify themselves and will be informed of the reference person for any problem or doubt related to the project. If participants in any of the groups have any questions or become distressed for any reason and need extra support, they will be able to contact a reference person through a telephone number that will be provided at the beginning of the study (included in the information sheet of the research). The study will have exhaustive compliance with all ethical-legal requirements in force related to research with humans. In the event that the CUMACA-M programme is shown to be effective in improving QOL and self-efficacy in LS-BC, after the investigation, the CG will be invited to obtain a username and password to access the programme for 9 months (See Supplementary Materials for information sheet form for participants.)

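### The 80% power in section 2.5 applies to quality of life alone, while section 2.10 requires both quality of life and self-efficacy to improve; power for that rule is not established

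*Protocol article*

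**What the plan says.** Section 2.5 (Sample Size) picks one outcome for the calculation: "For the calculation of the sample size, a primary outcome measure, quality of life (QOL), was selected". The inputs are given as "taking into account a difference in quality of life of 0.75 and a standard deviation of 1.8", and for the error rates "the type I error has been set at 5% and the type II error at 20" per cent. The result is 91 women per arm, 182 in all. Section 2.6 then plans 16 + 16 women in each of six centres and says: "This would be a total of 192 participants, which would cover the calculated sample size of 182 subjects".

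Section 2.10 (Data Analysis) sets the significance level at 0.05 in all cases and closes with the success rule: "The intervention will be considered effective if the two variables evaluated (quality of life and self-efficacy) show results of improvement in the intervention group" relative to control.

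The joint claim is not a slip in one sentence. The Abstract, the aim at the end of the Introduction and the hypothesis in section 2.1 all name both outcomes. Section 2.12 makes later access for the control group conditional on the same pair: "In the event that the CUMACA-M programme is shown to be effective in improving QOL and self-efficacy in LS-BC".

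The article gives no effect size, standard deviation, power or correlation with QOL for self-efficacy.

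**The concern.** A rule that needs success on two outcomes is harder to meet than a rule that needs success on one. The sample size and the type II error were worked out for the one-outcome question, but the trial will be judged on the two-outcome question. A reader who takes the 20% as the chance of missing a programme that works as planned will be too optimistic.

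The consequence is a programme with the full planned QOL effect being called not effective because self-efficacy missed significance. The control group's access (section 2.12) and the expected integration into primary care (section 4) both hang on that call.

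This is a conflict between two things the article states, so an unseen analysis plan would not remove it.

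**Working it through.** **Inputs from the article.** QOL difference 0.75 and SD 1.8, so d = 0.75/1.8 = 0.417 (the article rounds to 0.4); type I error 5%; type II error 20%; 91 per arm (section 2.5); 96 per arm planned (section 2.6: 6 × 16). Sidedness is not stated, but a two-sided test reproduces the sample size.

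**Inputs assumed.** Self-efficacy effect d₂; correlation ρ between the two outcomes, taken from 0 to 0.8; no losses unless stated.

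**Step 1: reproduce the plan's figure.**
n = 2 × (1.96 + 0.8416)² × (1.8/0.75)² = 90.4, so 91 per arm. This matches.

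**Step 2: power for QOL alone.** Power = Φ(d√(n/2) − 1.96).
- n = 91: 0.417 × √45.5 = 2.811; Φ(0.851) = 80.3%.
- n = 96: 0.417 × √48 = 2.887; Φ(0.927) = 82.3%.

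**Step 3: power for the two-outcome rule.** Read improvement as a significant result in favour of the intervention on each outcome. Joint power is then
P(Z₁ < d√(n/2) − 1.96 and Z₂ < d₂√(n/2) − 1.96),
with (Z₁, Z₂) standard bivariate normal with correlation ρ. It can never exceed the smaller of the two single-outcome powers, so it is at most 80.3% at 91 per arm and 82.3% at 96.

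At 91 per arm:

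| Self-efficacy d₂ | Power, self-efficacy alone | Joint, ρ = 0 | ρ = 0.5 | ρ = 0.8 |
|---|---|---|---|---|
| 0.3 | 52.5% | 42.2% | 47.8% | 51.3% |
| 0.417 (equal) | 80.3% | 64.4% | 69.1% | 73.2% |
| 0.5 | 92.1% | 73.9% | 76.6% | 78.9% |
| 0.6 | 98.2% | 78.8% | 79.6% | 80.2% |

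At 96 per arm with equal effects, joint power is 67.7% (ρ = 0), 71.9% (0.5) and 75.7% (0.8). If 10% of the 96 were lost (an assumed rate; the article gives none), these become 61.1%, 66.3% and 70.7%.

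**Step 4: what baseline adjustment would buy.** Adjusting an outcome for its T0 value, with baseline-to-follow-up correlation r, multiplies the residual SD by √(1 − r²), so d becomes d/√(1 − r²). With equal effects and ρ from 0 to 0.7:
- r = 0.5, 91 per arm: d = 0.417/√0.75 = 0.481; joint power 81–85%.
- r = 0.3, 91 per arm: d = 0.417/√0.91 = 0.437; joint power 70–76%.
- r = 0.5, 82 analysed per arm (about 10% lost from 91): joint power 76–80%.

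All figures rest on a two-group comparison of means, as section 2.5 does. They are not power figures for the MANOVA with group, time and interaction that section 2.10 plans.

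**The case against.** Several points on the other side carry weight.

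- **The stated 80% is not wrong.** Section 2.5 attaches it to QOL, where it reproduces. A reader might infer that the trial lacks its stated power or that the sample size is miscalculated. The article does not support that, because it never claims 80% for the joint rule.
- **The size of the shortfall is not known.** A reader might conclude that the true type II error is some definite figure well above 20%. That would need a self-efficacy effect that the article does not give. With d₂ near 0.6 the shortfall nearly vanishes; with 0.3 it is severe.
- **More than 91 per arm are planned.** With 96 per arm, joint power reaches 77–81% for d₂ = 0.5 and 81–82% for d₂ = 0.6, before losses. Section 2.5 also says the sample will be increased for losses. With equal effects, 96 per arm still falls short of 80%.
- **The rule does not say significant.** It asks only for results of improvement. If self-efficacy had only to move in the right direction, power at 91 per arm would stay at about 80% with equal effects. The 0.05 level set for all analyses, and the condition in section 2.12 that the programme be shown effective, make significance the likelier reading. The wording leaves it open.
- **Requiring both is legitimate.** It is a conservative choice and does not raise the type I error.

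These points limit how much can be said about size. They do not remove the mismatch between the outcome that was powered and the rule that decides.

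**Conclusion.** The point holds in a limited form. Sections 2.5 and 2.10 answer different questions: the 20% type II error is correct for QOL and is not the type II error of the trial's own success rule. Under the significance reading, joint power is at most the QOL power, and it comes close only if self-efficacy has a clearly larger standardised effect than QOL, which the article does not claim. With equal effects, a programme with the planned QOL benefit would miss the rule about 27–36% of the time at 91 per arm (100% minus 73.2% and 64.4%), and about 24–32% at 96 (100% minus 75.7% and 67.7%). Both ranges assume ρ of 0 to 0.8 and no losses. This is a power problem only.

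**What to change.** 1. In section 2.5, say that the 80% power is for QOL, and give the joint power for the section 2.10 rule with the self-efficacy effect and correlation it assumes. Section 2.5 already allows the sample size to be corrected after the pilot and before the trial starts. With equal effects and no adjustment, 80% joint power needs 119 (ρ = 0) down to 106 (ρ = 0.8) per arm before losses.
2. In section 2.10, define improvement as a significant between-group difference in favour of the intervention on each outcome.
3. Adjust each outcome for its T0 value. T0 is already collected in both arms (sections 2.8 and 2.9), so this needs no new data. It restores about 80% only if the baseline correlation is near 0.5, the effects are equal and losses are few.

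The cost is wording, one analysis choice and a less favourable stated power.

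Alternatively, QOL could decide effectiveness alone, with self-efficacy tested at 0.05 only if QOL is significant. That makes the existing sample size fit the rule, but it is more than an edit to section 2.10. The aim in the Abstract and Introduction, the hypothesis in section 2.1 and the condition in section 2.12 would all have to be brought into line. Whether that trade is worth making is for the investigators.

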### 2.11. Validity and Reliability/Rigour

This study is part of the Medical Research Council framework for the development and evaluation of randomized controlled trials for complex interventions in health. The invitation to participate in the study will always be made by the same researchers and, once the consent is signed, the random assignment will be made to the CG or the IG. Similarly, the initial session in both groups will be conducted by trained nurses who are knowledgeable about the research protocol.

As informed earlier, the instruments that will be used for data collection (QOL-CS and SEMCD) are validated and translated into Spanish and are the most widely used for the targeted population group.

In the IG, the questionnaires will be integrated into the CUMACA-M programme itself and, in the CG, an online electronic tool will be used for their collection. The research consists of a plan for the management and treatment of participants’ data, in which the method of data collection, its custody, and the restriction of access to authorized research team personnel is indicated. This plan was developed with advice from the Data Protection Officer of the Public University of Navarra.

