### 2.7. Description of the CUMACA-M Intervention

The personalized digital intervention will be designed in web and mobile application format to facilitate access at any time and from any place, regardless of the device used (computer, tablet, or smartphone). As it is a personalized intervention with the use of different algorithms using artificial intelligence, participants will receive information adapted to their personal needs. As mentioned above, the contents will be developed from an exhaustive review of recommendations and clinical practice guidelines for the care of LS-BC and on the main needs of LS-BC (Phase I of the MRC). Subsequently, the content of the intervention will be agreed upon by a panel of multiprofessional experts from PHC and specialized care, as well as an LS-BC and a representative of an association supporting women with breast cancer.

These contents will be configured in different modules according to the areas identified as priority needs of the LS-BC (for example, fatigue module, lymphedema module, work activity module, and fear of recurrence module), and the principles of the educational intervention characteristic of PHC consultations will be followed (feedback methods, risk personalization, increased awareness, active learning, persuasive communication, goal setting, and actions) [30].

The main page of the digital intervention programme will show a personal record and a video on how to use the programme. The intervention will begin with a screening questionnaire that will measure several concepts that impact quality of life, such as fatigue, anxiety, fear of recurrence, or return to work. According to the responses, participants will receive personalized advice by means of artificial intelligence algorithms on which modules deserve more attention. The web application itself will integrate the measurement of outcome variables that will allow evaluation of the effectiveness of the intervention. The effective management of the topics identified for the intervention will ultimately improve the quality of life of the LS-BC.

In Phase II (feasibility and piloting), the pilot of the intervention will be carried out through a pre-experimental pretest–post-test design with a single group that will pilot the intervention and test the usability of the application to identify areas for improvement and introduce timely modifications.

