### 2.9. Data Collection

The intervention group protocol is as follows: the CUMACA-M programme is based on a web application for long-term breast cancer survivors. Participants (LS-BC) in the IG will receive the personalized digital intervention (CUMACA-M programme). Coinciding with the initial session of acceptance to participate in the project and signing a consent form, after the random assignment to the IG, the web application will be presented. Registration will be performed (with username and password), and instructions for use will be provided. At that time, preintervention and sociodemographic data will be collected, as well as measurements of QOL and self-efficacy in the management of the disease. Medical data will be collected in an electronic questionnaire with the help of the SurveyMonkey^®^ tool. For this, a duration of one hour in a face-to-face session is estimated. Subsequent measurements of QOL and self-efficacy variables will be performed at T1, T2, and T3, from the beginning of the intervention. Through the web application, a message will be sent to participants prompting them to complete the questionnaire. This reminder will be reinforced by email and through a WhatsApp^®^ distribution list (differentiated lists for LS-BC of the IG and CG). Satisfaction data with the web application will be collected only at 9 months (T3).

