The control group protocol consists of standard care in the PHC nursing office. Since there are no defined nursing care procedures for long-term cancer survivors in PHC in Spain, the LS-BC in the CG will be limited to a single face-to-face consultation of an estimated duration of 1 h, in which participants will receive an informative brochure on topics related to life after cancer and will take the opportunity to offer brief advice on healthy lifestyle habits regarding the importance of a balanced diet and regular exercise. In this session, information about the study will also be provided and, after acceptance to participate, information about the variables to be collected over time (T0, T1, T2, and T3) will be explained. The sociodemographic and medical data of the LS-BC will be collected in T0, as well as the data for the QOL and self-efficacy variables in the management of the disease. An electronic questionnaire will be designed with the help of the SurveyMonkey^®^ (Momentive, San Mateo, CA, USA, 2022) tool to be completed during the consultation on a tablet. Subsequently, participants will be contacted by email and a WhatsApp^®^ (2.22.20.75, Meta Platforms, Menlo Park, CA, USA, 2022)) distribution list with an invitation to complete a questionnaire that will evaluate their QOL and self-efficacy at T1, T2, and T3. Satisfaction data with the care received (standard nursing care) will be collected at 9 months (T3).

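### Outcome collection and prompting differ by arm (in-app for the intervention group, separate online tool for controls), so they cannot be separated from treatment

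*Protocol article*

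**What the plan says.** **Intervention group.** Section 2.7 makes the application a measuring instrument as well as the treatment: "The web application itself will integrate the measurement of outcome variables that will allow evaluation of the effectiveness of the intervention". Section 2.11 repeats this and sets the control procedure beside it: "In the IG, the questionnaires will be integrated into the CUMACA-M programme itself and, in the CG, an online electronic tool will be used". For T1 to T3, section 2.9 says: "Through the web application, a message will be sent to participants prompting them to complete the questionnaire". It then adds two outside channels: "This reminder will be reinforced by email and through a WhatsApp" list. In this arm the survey tool is named only for clinical data: "Medical data will be collected in an electronic questionnaire with the help of the SurveyMonkey" tool. Section 2.9 places the T0 measurement of QOL and self-efficacy in the face-to-face session after assignment, but does not name the tool.

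**Control group.** At T0, section 2.9 says: "An electronic questionnaire will be designed with the help of the SurveyMonkey" "tool to be completed during the consultation on a tablet". For T1 to T3 the women are invited by email and a WhatsApp list. The later form is not named there; section 2.11 calls it an online electronic tool.

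**Analysis.** Section 2.10 plans a MANOVA with group, time and their interaction over T0 to T3, and calls the programme effective if both QOL and self-efficacy improve relative to control. Neither that section nor the limitations in section 3 mentions the difference in collection.

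**The concern.** The same instruments reach the two arms by different routes, and the route is fixed by the arm. The women know which care they received, and both outcomes are their own ratings. Intervention women give those ratings inside the product being judged. If that setting, or the extra prompt, shifts answers or response, the shift appears as a treatment difference, and no later analysis can remove it because no participant has one arm's treatment with the other arm's tool.

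The second issue is who answers. In the intervention group the questionnaire sits in the programme, so response may depend on whether a woman still uses it. Engagement is itself a consequence of assignment. Loss related to it could make the responders in one arm differ from those randomised in a way that the other arm does not share.

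**Working it through.** **1. The two procedures side by side**

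| | Intervention group | Control group |
|---|---|---|
| QOL-CS and SEMCD at T0 | tool not named in 2.9; 2.7 and 2.11 imply the app | SurveyMonkey on a tablet (2.9) |
| QOL-CS and SEMCD at T1–T3 | in the app (2.7, 2.11) | online electronic tool (2.9, 2.11) |
| Prompts at T1–T3 | in-app message, email, WhatsApp (2.9) | email, WhatsApp (2.9) |

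An indicator for tool would equal the indicator for arm from T1 on, so the two are not separately estimable.

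**2. The plan's own sample size**

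Inputs from section 2.5: difference 0.75, SD 1.8, type I error 5% (two-sided assumed), power 80%.

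n per arm = 2 × [1.8 × (1.960 + 0.842) / 0.75]² = 90.4, rounded up to 91. This reproduces the stated 91. The sample size is not in question here; the difference and SD set the scale for what follows.

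**3. When a platform shift cancels**

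Let b be a constant shift from answering in the app and δ the true effect on change.

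- T0 and follow-up both in the app: the intervention group's change contains b − b = 0, so the interaction estimates δ.
- T0 outside the app, follow-up inside: the change contains b, so the interaction estimates δ + b.

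In the first case the main effect of group still carries b. A shift that grows with exposure to the programme does not cancel in either case.

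**4. Size of an uncancelled shift (b is assumed)**

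A single between-arm comparison of QOL, two-sided normal test, 91 per arm: SE = 1.8 × √(2/91) = 0.267. With no true effect, the chance of significance is P(|Z + b/SE| > 1.96).

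| Assumed b | b/1.8 | Share of 0.75 | False-positive rate |
|---|---|---|---|
| 0 | 0 | 0% | 5% |
| 0.10 | 0.06 | 13% | 6.6% |
| 0.18 | 0.10 | 24% | 10.4% |
| 0.36 | 0.20 | 48% | 27% |

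A shift of 0.20 against the intervention group would cut power for a true 0.75 from 80% to 54%.

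**5. Size of differential loss (rates and gap are assumed)**

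Sections 2.5 and 2.6 give no loss rate; 192 planned against 182 needed leaves 1 − 182/192 = 5.2%. In a complete-case comparison the bias is the gap between responders and non-responders, multiplied by the difference in missing shares. Take 96 randomised per arm, with loss of 30% in the intervention group and 10% in the control group (67 and 86 remaining).

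- Gap 0.9: 0.9 × (0.30 − 0.10) = +0.18; false-positive rate about 9%.
- Gap 1.8: 1.8 × (0.30 − 0.10) = +0.36; false-positive rate about 23%.

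Reverse the loss rates and the bias becomes −0.18 or −0.36. Taking T0 in the app does not remove this bias.

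All these rates are for QOL alone. The rule in section 2.10 also requires self-efficacy to improve, so they are not the error rate of the full decision.

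**The case against.** Both routes are electronic self-completion of the same instruments, and T0 is taken in a face-to-face session in each arm, so a pure platform effect may be small. If the intervention group's T0 is in the app, as sections 2.7 and 2.11 suggest, a constant shift drops out of the interaction. Email and WhatsApp reach both arms. The pilot of 20 women will test usability, and methods for missing data may lie in an analysis plan that is not shown. Every magnitude above rests on assumed inputs.

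Much of this stands, and it limits the point. A reader might infer that disengaged women would be lost in the intervention group only, and that the bias must favour the programme. The article does not support that. Control women, who have one consultation and then only survey invitations, can also stop answering; intervention women who leave the app are still reached by email and WhatsApp; and the extra prompt may raise their response. Nor does the article say whether an outside reminder links straight to the form, or what surrounds the questionnaire on screen.

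What does not fall away is the stated asymmetry itself. The cancellation depends on a T0 tool that section 2.9 does not name, and it does not cover a shift that changes over time or selective loss. A single-group pilot cannot detect a difference between arms. The absence of missing-data methods is not counted against the article.

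**Conclusion.** The point holds as a flaw in the measurement procedure. The protocol fixes a different collection tool and a different set of prompts in each arm for two unblinded self-reported outcomes, and the planned MANOVA cannot tell these apart from treatment. Engagement-related differential missingness is a risk of this set-up, not a stated fact, and it could push the result either way.

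The size is unknown. For QOL, an uncancelled shift of 0.10 to 0.36 points would raise the false-positive rate from 5% to about 7% to 27%, assuming no true effect, 91 per arm, SD 1.8 and a single two-sided comparison. The shift itself is assumed, not taken from the article. The stated 91 per arm is correct on its inputs and needs no change. The confounding cannot be undone once data are collected, so it should be settled before enrolment.

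**What to change.** - Collect QOL-CS and SEMCD at T0, T1, T2 and T3 in both arms with the same stand-alone electronic questionnaire. SurveyMonkey is already named for control-group data and for medical data in the intervention group.
- Use the same reminder channels, number and timing in both arms: email and WhatsApp, without the in-app message.
- Keep the app's screening questionnaire for tailoring only.
- Amend sections 2.7, 2.9 and 2.11 to match, and name the T0 tool for both arms.
- Report response by arm and visit.

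Cost: intervention women open one link outside the app and lose the in-app prompt, which may slightly lower their completion. The survey tool is already in use, so the added work is small. Unblinded self-report remains, because it is inherent in this comparison.
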